### The GCCRQ

The GCCRQ questionnaire was developed and implemented by the Global Consortium for Chemosensory Research to assess whether and how COVID-19 infection affects sense of smell, taste, and chemesthetic sensitivity [12]. Participants are asked about their COVID-19 testing status and symptoms, and they complete 18 items relating to their sense of smell, taste, chemesthetic ability, and food flavors before, during, and after COVID-19 illness. Due to the potential for additional participant burden, the completion of this questionnaire is optional and will not affect the study participation. For participants who complete the GCCRQ, we will ascertain the extent to which the measures obtained using this approach correlate with the measures in the study.

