### Common Household Item Smell Test

For comparison with the SSTT, participants will be asked to complete a daily assessment of smell using household items (see Multimedia Appendix 2). To assess the participants’ olfactory sensitivity, we will provide them with 6 categories of common household items. Participants will be asked to choose one odor from a drop-down menu for each category and indicate their perception of it on a scale from “absent” to “heightened.” This approach is based on a previously reported self-assessment measure of smell sensitivity using household items [32], with an additional category of stimuli that are particularly high in trigeminal irritation. The items for all categories were adjusted to include culturally appropriate household items that are common in Singapore.

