### Primary Outcomes

The primary outcomes are (1) to measure the onset, severity, duration, and recovery of changes to smell and taste sensitivity resulting from COVID-19 infection and (2) to assess the efficacy of the SSTT as a simple diagnostic approach. Data will be used to test the association of smell and taste loss with positive COVID-19 infection, measuring changes in sensory acuity from baseline (initial screening, Day 0) to the end of the 4-week monitoring period, to investigate the best predictors of recovery of smell and taste sensitivity. In addition, the primary methodological outcome is a comparison of the consistency and discriminability of self-assessment standardized home use tests compared to both the common household items home use test and the questionnaire-based measures. The findings will inform best practice approaches for future self-assessment of smell and taste acuity among people with suspected COVID-19 infection. This will be measured directly via responses to the daily home-use smell and taste test, complemented by measures from the self-reported questionnaire responses (SSTQ, SNOT-22, GCCRQ).

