### Statistical Analysis

Using a case-control study design for people testing positive (case) or negative (control) for COVID-19 infection, data will be collected on changes in smell and taste loss that have occurred in the 2 weeks prior to the COVID-19 test and on smell and taste acuity changes measured on a daily basis for up to 28 days following the COVID-19 test. The data will be used for descriptive comparisons of the onset, duration, and severity of smell and taste changes with COVID-19 infection and to report on the incidence of these changes among participants testing positive for COVID-19 infection (and those recovering from infection).

Logistic regression analysis will be used to estimate the odds ratio for loss of smell and taste sensitivity as a predictor of testing positive for COVID-19 infection. This will also enable comparison of smell and taste loss as a predictor of COVID-19 infection compared to other symptoms, such as fever and dry cough. Pearson correlations will be used to investigate relationships between smell and taste changes and other symptoms. Time-series analysis of variance (ANOVA) models will be run to investigate temporal changes in smell and taste ratings over time, with baseline ratings in smell and taste acuity corrected for at an individual level. Linear mixed models will be used to test for significant differences in smell and taste acuity between groups, with participants stratified by their COVID-19 infection status.

Factor analyses, using oblique rotation and baseline home-use test responses (conducted in-clinic), will be conducted to assess the internal consistency of our smell and taste test. Adjusted odds ratios will be calculated to investigate the best predictors of recovery of smell and taste acuity postinfection. Linear regression will be run to examine whether responses to the smell and taste test predict responses to the household item odor test (smell) and self-reported taste acuity, respectively. Regression analyses will be conducted to investigate the association between loss of smell and taste acuity and self-reported appetite and food-related quality of life. All statistical analyses will be completed using SPSS (IBM Corporation).

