## Discussion

### Study Overview

This study will longitudinally track the onset, severity, and recovery of changes in chemosensory (smell and taste) acuity among people with and without COVID-19 infection (following swab testing) using standardized assessment tools that can be used in a residential setting. The objectives of this study are to confirm the association between sudden changes in smell and taste sensitivity and COVID-19 infection in an at-risk population in Singapore; to establish the temporal onset, severity, and recovery of changes in smell and taste sensitivity with COVID-19 infection; to evaluate the efficacy of the SSTT as an early diagnostic tool; and to investigate the effects of loss of smell and taste acuity on appetite and food-related quality of life.

Using a longitudinal prospective study design, we aim to establish the association of the onset, severity, and recovery of smell and taste changes with COVID-19 infection while also providing an initial validation of a rapid, cost-effective, self-administered, and standardized approach to tracking spontaneous changes to taste and smell sensitivity in both clinical and residential settings. These findings will enable better identification of asymptomatic or pre-symptomatic carriers of COVID-19 infection, encouraging earlier self-isolation and medical consultation. Currently, a small number of studies have objectively tested smell and taste acuity in patients with COVID-19, with the majority of studies relying on subjective self-report measures [29]. Given that one-time self-report measures may underestimate the prevalence of olfactory impairment [36,37] and fail to capture temporal changes in sensory acuity, the COVISMIA-19 study provides an objective measurement of smell and taste loss in a sample of patients with COVID-19 that can encourage earlier self-isolation and medical consultation. Furthermore, current household item tests of smell and taste acuity are often not standardized and are heavily reliant on stimuli availability and volunteer compliance [32,33]. The COVOSMIA-19 approach will provide a short, easy-to-use, self-administered test approach that standardizes the smell and taste stimuli and can be easily completed by participants in their own home.

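### The stated instrument analyses measure association and SSTT structure, so they do not deliver the head-to-head comparison of consistency and discriminability named as the primary methodological outcome

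*Protocol article*

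**What the plan says.** The Primary Outcomes section states that "the primary methodological outcome is a comparison of the consistency and discriminability of self-assessment standardized home use tests compared to both the common household items" and, as the sentence continues, "home use test and the questionnaire-based measures". It also lists the SSTT's value as a diagnostic approach among the primary outcomes. The Study Overview repeats the aim: "to evaluate the efficacy of the SSTT as an early diagnostic tool". The household test is in the study for this purpose: "For comparison with the SSTT, participants will be asked to complete a daily assessment of smell using household items".

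Three analyses of the instruments are named:

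- **Factor analysis** (Statistical Analysis): "Factor analyses, using oblique rotation and baseline home-use test responses (conducted in-clinic"), which "will be conducted to assess the internal consistency of our smell and taste test".
- **Linear regression** (Statistical Analysis): "Linear regression will be run to examine whether responses to the smell and taste test predict responses to the household item odor test (smell"), with self-reported taste acuity as the outcome on the taste side.
- **Correlation with the optional GCCRQ** (The GCCRQ): "we will ascertain the extent to which the measures obtained using this approach correlate with the measures in the study".

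The Statistical Analysis section also plans a logistic regression of swab result on smell and taste loss, and mixed models of acuity by infection status. Neither names the instrument that supplies the smell or taste variable. The only comparison stated for the logistic model is with other symptoms, such as fever and cough.

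**The concern.** The outcome is comparative. To answer it, the same quantity has to be estimated for at least two instruments and the two estimates set against each other. The stated analyses instead describe how SSTT responses group together on one day and how strongly they go with other measures.

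Two tests of the same sense should be associated unless one of them fails badly. A significant slope is therefore the expected result under almost any ranking of the tests. The article says the findings will guide best practice for future self-assessment. If a significant slope were read as support for preferring the SSTT, that advice would rest on a result unable to distinguish a better test from a worse one.

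**Working it through.** The plan gives no figure for the instrument comparison, so there is none to reproduce. Its one sample size, 235, was derived for the logistic regression.

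**Step 1. Outcome against analysis.**

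| Needed for the stated outcome | Stated analysis | What it gives |
|---|---|---|
| Consistency, SSTT v household test | Factor analysis, SSTT only, Day 0 | Internal structure of the SSTT; no household value, no day-to-day value |
| Consistency, SSTT v questionnaires | None | – |
| Discriminability, SSTT v household test | Linear regression of household odour responses on the SSTT | Association |
| Discriminability, SSTT v questionnaires | Regression of self-reported taste acuity on the SSTT; GCCRQ correlation | Association |
| Discrimination by PCR status | Logistic and mixed models | No instrument named; no contrast between instruments |

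The household test cannot enter the Day 0 factor analysis as scheduled. It is described only as a daily assessment, and neither the in-clinic column of Table 1 nor the in-clinic minimum in Data Management lists it. Self-reported smell, the SSTQ smell items and the SNOT-22 have no specific analysis against the SSTT.

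**Step 2. Can the regression rank the tests?** As described, it contains the responses to the two tests. It contains neither the PCR result, which discrimination needs, nor a repeat of the same test in the same person, which consistency needs. The slope is in household-scale units per SSTT unit, so its size depends on the two scales.

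**Step 3. Illustration (all effect sizes assumed).** Take one score per test, with SD 1 within each PCR group. Let the positive fraction be π = 0.20, a value borrowed from the sample-size section. Positives are shifted by d_S on the SSTT and d_H on the household test. The within-group correlation between tests is ρ and the within-group retest reliability is rel. Then π(1−π) = 0.16 and:

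- Var = 1 + 0.16 d²
- Cov = ρ + 0.16 d_S d_H
- R² = Cov² / (Var_S × Var_H)
- slope = Cov / Var_S
- AUC = Φ(d/√2)
- retest correlation = (rel + 0.16 d²) / (1 + 0.16 d²)

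*A, SSTT better* (d_S 1.2, d_H 0.4, rel 0.8 and 0.5, ρ 0.5):
- Var_S = 1.2304, Var_H = 1.0256, Cov = 0.5 + 0.0768 = 0.5768
- R² = 0.3327/1.2619 = 0.264; slope = 0.5768/1.2304 = 0.47
- AUC: Φ(0.849) = 0.80 against Φ(0.283) = 0.61
- Retest: 1.0304/1.2304 = 0.84 against 0.5256/1.0256 = 0.51

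*B, household test better* (A with the tests exchanged):
- R² = 0.264; slope = 0.5768/1.0256 = 0.56
- AUC 0.61 against 0.80; retest 0.51 against 0.84

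*C, equal* (d 0.8, rel 0.65, ρ 0.475 for both):
- Var = 1.1024, Cov = 0.475 + 0.1024 = 0.5774
- R² = 0.3334/1.2153 = 0.274; slope = 0.52
- AUC Φ(0.566) = 0.71; retest 0.7524/1.1024 = 0.68

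A simulation of 400,000 participants per scenario agreed (R² 0.263, 0.263 and 0.274).

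**Step 4. Significance.** If all 235 contributed, t = √[R²/(1−R²) × 233]. This is √(0.358 × 233) = 9.1 in A and B, and √(0.378 × 233) = 9.4 in C. The test is overwhelmingly significant in all three.

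**The case against.** The best defence is that this is an article condensing a fuller plan, and that cut-offs, ROC curves and reliability coefficients usually sit in the fuller document. The logistic and mixed models bear on discrimination by PCR status and could be run once per instrument. Regression on an established measure is a recognised part of validation, and the Study Overview claims only an initial validation.

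Much of this stands, and it rules out several stronger readings that a reader might infer:

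- *That the outcome cannot be answered.* The SSTT and household test are both daily, the SSTQ and SSTT are both done on Day 0, and swab status is linked. The data would support the comparison, and a fuller plan may contain it.
- *That R² is always the same in either direction.* This holds for one score against one score. The SSTT has two odours and the household test six categories; with several predictors R² is not symmetric. The argument in Step 2 does not depend on symmetry.
- *That factor analysis says nothing about consistency, or that smell has only two indicators.* Loadings are relevant to internal consistency. Participants both identify and rate each odour, so two odours give four responses. The valid limit is one instrument on one day.
- *That the plan claims superiority of the SSTT.* The hypotheses in the Introduction concern sensory loss, recovery, appetite and food-related quality of life; the outcome says comparison.
- *That the odds ratio of 1.723 shows poor discrimination.* It belongs to the logistic regression and does not measure this problem.

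The defence does not remove the mismatch. The article does not leave the instrument analyses open: it names them and says what they are for, and they do not match the outcome it names.

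**Conclusion.** The concern holds as a mismatch between a stated primary methodological outcome and the analyses stated for it. None of the named analyses estimates consistency or discriminability for two instruments and compares them. The gap is widest for the questionnaires and for day-to-day consistency.

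The conclusion that association does not rank the tests follows from what the regression contains. The R² values illustrate it and rest on assumed effects, single scores and 20% positives; they are not predictions for this study. The verdict also takes discriminability to mean separating PCR-positive from PCR-negative participants. The article does not define the term, although its diagnostic aim points that way.

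**What to change.** Keep the regression and correlation as convergent validity and the factor analysis as internal structure, and label them so. Define discriminability, say which questionnaire scores are comparators, and add a head-to-head analysis.

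- **Discriminability.** Estimate each instrument's AUC for PCR status in the same participants at the same time, with the paired difference (DeLong) and its confidence interval. Compare the SSTT with the SSTQ self-rating at Day 0. Compare the SSTT smell score with the household smell score at the first home session; the household test covers smell only, so taste items must be left out. Report sensitivity and specificity at a pre-specified cut-off.
- **Consistency.** Compare within-person day-to-day reliability of the SSTT smell score and the household score in PCR-negative participants who report no change in smell. Give the ICC together with the within-person SD on a standardised scale, because the ICC falls when people in a stable group differ little. Restrict to, or adjust for, days on which the same household items were chosen, so that a change of item is not counted as unreliability.

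The cost is a few analyses on data already planned. The drawback is wide intervals if PCR-positive participants are few; their number is not given.

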### The SSTT

Participants will be provided with their own standardized home-use smell and taste test that they will complete daily for up to 28 consecutive days (Multimedia Appendix 2). The questioning approach is based on that used in the Yale School of Medicine “Jiffy” Test of mell Sensitivity [35], in which respondents perform a similar procedure with Jif peanut butter.

The SSTT smell test includes two odors—a food odor (mango) and a nonfood odor (detergent)—both of which consist of odor mixtures that have been formulated by an international fragrance manufacturer (Symrise AG). The odor mixtures were chosen to avoid possible specific anosmias to individual odor compounds, and the odors are dosed at the suprathreshold level in specialized odor delivery pens (Otto Hut). Both fragrances have been tested to deliver a suprathreshold odor at a consistent intensity and stability for the duration of the home-use test period. To perform the test, the participants remove the pen lid and place the pen 3 inches from their nose while breathing normally. For each smell, participants will identify the smell and rate the perceived intensity on a visual analog scale (VAS) from “not strong at all” to “extremely strong smell.”

For the daily taste test, participants will be provided with small quantities of powder selected to represent the four prototypical tastes: “sweet” (table sugar, NTUC FairPrice), “salty” (table salt, NTUC FairPrice), “bitter” (granulated coffee powder, Nescafé), and “sour” (lime powder, Knorr). The participants will be instructed to take a small amount of each item in a sequential monadic order on the tip of their tongue with a small spoon; they will then be asked to identify and rate the perceived intensity of the taste on a VAS from “not strong at all” to “extremely strong taste” through a web-based questionnaire completed on their smartphone or other device. The participants will be asked to rinse with water between each taste stimulus and will be provided with sufficient taste stimuli for the 28 days of assessment.

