### Additional Questions

Once per week, participants will complete an additional set of questions (Day 7, 14, 21, and 28) relating to their enjoyment of food, appetite, weight, and food-related quality of life (eg, “I no longer enjoy cooking/preparing food”). The goal of this questionnaire is to assess the relative impact of changes in sensory acuity with self-reported appetite and food enjoyment, as it may be related to weight fluctuations observed during the period of infection.

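### The planned linear regression of household-item smell ratings on SSTT ratings does not fit daily repeated data and cannot show that the two tests track change together

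*Protocol article*

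**What the plan says.** In the protocol article, the Statistical Analysis section names one analysis that joins the two smell tests: "Linear regression will be run to examine whether responses to the smell and taste test predict responses to the household item odor test". It gives no person effect, clustering, day or unit of analysis.

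Both variables are repeated measures. Under Common Household Item Smell Test, "participants will be asked to complete a daily assessment of smell using household items". Under The SSTT, each participant receives a "standardized home-use smell and taste test that they will complete daily for up to 28 consecutive days". Both are subjective ratings: a visual analog intensity scale for the SSTT, and a scale from absent to heightened for the household items.

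The comparison matters to the study. Primary Outcomes says "the primary methodological outcome is a comparison of the consistency and discriminability of self-assessment standardized home use tests" against the household test and the questionnaires, and says it will be measured directly through the daily home responses. The Introduction lists evaluation of the SSTT against household-item measures as a primary objective, and describes the comparator as measured changes in acuity.

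The same Statistical Analysis section does specify structure for other analyses: linear mixed models for the group comparison, individual baseline correction for the time-series ANOVA, and in-clinic baseline data for the factor analyses. It attaches none of these to this regression.

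**The concern.** Linear regression takes its rows as independent. Up to 28 ratings from one person are not independent if people differ in their usual level, so a pooled analysis would give p-values that are too small and intervals that are too narrow.

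There is a second difficulty. The slope mixes two things: whether a person's household rating falls on days when the SSTT rating falls, and whether people who rate high on one scale also rate high on the other. The stated interest is in change over time, which is the first. A significant slope would probably be read as evidence that the SSTT follows smell loss and recovery as the household test does, although it could arise entirely from the second.

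**Working it through.** **The plan's own figure.** The article gives no figure for this regression. Its sample size of 235 belongs to the logistic regression. It reproduces as 234.6 with a variance-corrected Wald formula, one-sided 5%, 95% power, baseline probability 0.20 and odds ratio 1.723. It is used here only as the N for simulation.

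**Inputs from the article.** N = 235 (Sample Size Determination); 69 recruited by October 2, 2020 (Results); up to T = 28 days. People with fewer than 25% of tests leave the longitudinal analyses (Data Management), so the floor is 0.25 × 28 = 7 days.

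**Assumptions not in the article.** Intraclass correlation (ICC) of daily ratings 0.3, 0.5 or 0.7 for both tests; true within-person association zero; person-level correlation between the tests of 0, or 0.1 to 0.5 to represent shared scale use.

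**Reading A: person-days pooled, person levels unrelated.** The true variance of the slope exceeds the regression's own variance by the factor

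D = 1 + (T − 1) × ICC(SSTT) × ICC(household),

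and the actual two-sided error rate is 2 × [1 − Φ(1.96/√D)]. For T = 28 and ICC 0.5: D = 1 + 27 × 0.25 = 7.75; 1.96/√7.75 = 0.704; error rate 0.48.

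| Days | ICC 0.3 | ICC 0.5 | ICC 0.7 |
|---|---|---|---|
| 7 | D 1.54, 11% | D 2.50, 22% | D 3.94, 32% |
| 14 | D 2.17, 18% | D 4.25, 34% | D 7.37, 47% |
| 28 | D 3.43, 29% | D 7.75, 48% | D 14.23, 60% |

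Simulation with N = 235 (2000 runs per cell) agrees within about one percentage point. Correct intervals would be √D times as wide, from √1.54 = 1.24 to √14.23 = 3.77.

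**Reading B: one mean per person.** With person levels unrelated, the simulated error rate is 4% to 6%, so the repeated-rows problem disappears. Now let person levels correlate while day-to-day changes stay unrelated (28 days, ICC 0.5, 1000 runs). The percentages of significant results are:

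| Person-level correlation | Pooled, N = 235 | Person means, N = 235 | Person means, N = 69 | Person-centred, both N |
|---|---|---|---|---|
| 0.1 | 81 | 32 | 13 | 5.5 |
| 0.2 | 99 | 86 | 37 | 5.1–5.2 |
| 0.3 | 100 | 99 | 68 | 4.8–4.9 |
| 0.5 | 100 | 100 | 98 | 4.5–4.8 |

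Person means therefore often give a significant slope when the tests do not move together at all. Only the person-centred slope answers the tracking question at about the nominal rate.

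**Autocorrelated days.** The tables assume that daily deviations are independent. With an assumed lag-1 correlation of 0.5, a person-centred slope with ordinary standard errors still rejected 10% to 13% at 28 days. With person-clustered standard errors, it rejected 4% to 7% across lag-1 correlations of 0 and 0.5. The replacement model therefore needs an error structure for days as well as a person term.

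**The case against.** The strongest reply is that pooling is inferred. The article says linear regression and nothing about rows, and an article may leave the unit of analysis to a fuller document. The Data Management section also describes listwise deletion as removing an individual's data, which fits one record per person at least as well as one per day. This stands: the 11% to 60% range is conditional on pooling, and a reader should not infer that the plan commits to it.

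Second, with correlated person levels, SSTT ratings really do predict household ratings between people, so the high rejection rates are power for a real association. This also stands. Between-person agreement is a legitimate question, and those rates are false positives only for a claim of within-person tracking. The two scales also have different anchors, so the amount of shared scale use is unknown.

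Third, a reader might extend the criticism to the neighbouring regressions. The documents do not support that. For appetite and quality of life the text is "Regression analyses will be conducted to investigate the association between loss of smell and taste acuity and self-reported appetite and food-related quality of life", which names no model type. Table 1 and the SSTQ section show Day 0 values as well as weekly ones. Self-reported taste is likewise rated at Day 0, when the in-clinic SSTT is also done. Either could be a one-row analysis.

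Last, Table 1 has no household-item row at all, so its silence about the clinic visit proves nothing. The daily frequency rests on the household-test section, which states it plainly.

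What the reply does not answer is that a reduction to one row per person still cannot address change, which is the subject of the comparison.

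**Conclusion.** The point holds for one regression, SSTT against household-item smell ratings. The model named does not suit the data under either reading. Pooled rows would give an actual error rate of about 11% to 60% at a nominal 5%. One row per person would give a valid test of between-person agreement only.

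The sizes rest on assumed ICCs of 0.3 to 0.7 and on 7 to 28 completed days. The inflation exceeds 5% throughout that range, and the closed form does not depend on N. The shared-scale-use figures rest on assumed person-level correlations.

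No sample size or stated decision rule depends on this p-value. The regression is, however, the only named analysis linking the SSTT to the household test under the primary methodological outcome, so it should be changed before the analysis is run.

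**What to change.** In the Statistical Analysis section, replace this one regression with a linear mixed model for the daily household-item rating. Include a participant random intercept and either a first-order autoregressive residual or person-clustered standard errors. Enter the SSTT smell rating as two terms: the person's mean over the analysed days, and each day's deviation from that mean. State that any claim that the SSTT tracks change as the household test does rests on the deviation term. Report the person-mean term separately as between-person agreement.

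For the self-reported taste and the appetite or quality-of-life regressions, state whether Day 0 or repeated data are used. Apply the same model only if the daily or weekly repeats are analysed.

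This changes analysis wording only. No further data are needed, and linear mixed models in SPSS are already planned. The price is wider confidence intervals, some associations that may lose significance, and a little more analysis work.

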The COVOSMIA-19 study will standardize the smell and taste stimuli used by all participants to ensure consistency and provide a disposable, rapid, self-administered home use test, the Singapore Smell and Taste Test (SSTT), to minimize the risk of cross-contamination and infection spread. The trial will enable self-testing for up to 28 consecutive days and will provide a standardized longitudinal assessment of smell and taste function to enable tracking of the onset, severity, and recovery of the sensory changes reported to occur with COVID-19 infection. The standardized smell and taste test will also be compared with self-reported questionnaire measures of smell and taste changes and measured changes to sensory acuity using common household items (an approach previously used by [32]).

The primary objectives of this study are to (1) assess the prevalence of sudden changes in smell and taste sensitivity with COVID-19 infection in a population at risk for COVID-19 infection in Singapore, (2) establish the temporal onset, severity, and recovery of changes in smell and taste sensitivity with COVID-19 infection, and (3) evaluate the efficacy of the SSTT as a rapid, cost-effective, self-administered measure of changes to smell and taste compared to previous measures using household items. The secondary objective of this study is to investigate the effects of loss of smell and taste acuity on food enjoyment and appetite as well as to establish the impact of COVID-19 infection on food-related markers of quality of life. We hypothesize that loss of smell and taste acuity will be associated with COVID-19 infection, will return upon recovery from infection for the majority of patients, and will result in short-term reductions in appetite, food enjoyment, and food-related quality of life.

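### The primary methodological outcome promises a comparison of consistency and discriminability between instruments, but the between-instrument analyses named measure only agreement and cannot show which test is better

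*Protocol article*

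**What the plan says.** Primary Outcomes (Methods) sets the methodological outcome as "a comparison of the consistency and discriminability of self-assessment standardized home use tests compared to both the common household items home use test"; the questionnaire-based measures are a second comparator. It states the purpose: "The findings will inform best practice approaches for future self-assessment of smell and taste acuity among people with suspected COVID-19 infection". The Introduction lists a matching primary objective, to judge how well the SSTT performs relative to household-item measures used before, and says that the SSTT will also be compared with self-reported questionnaire measures.

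Statistical Analysis names these relevant analyses:

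- For the SSTT and the household test: "Linear regression will be run to examine whether responses to the smell and taste test predict responses to the household item odor test (smell". The same sentence pairs SSTT taste with self-reported taste acuity.
- A factor analysis of the in-clinic baseline SSTT responses, which "will be conducted to assess the internal consistency of our smell and taste test". No other instrument enters it.
- A logistic regression of swab result on loss of smell and taste, compared with other symptoms such as fever and cough. No instrument is named.
- Linear mixed models comparing acuity by infection status, also without naming an instrument.

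The GCCRQ section adds that, among those who complete this optional questionnaire, its measures will be correlated with the study measures.

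**The concern.** A comparison of consistency and discriminability needs a value of each property for each instrument, and then a difference. No analysis named in the article is described as producing that. The analyses that join two instruments ask only whether they move together.

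The direction of the regression adds to the difficulty. The dependent variables are of kinds about which the protocol itself has reservations. Of household tests it says that "current household item tests of smell and taste acuity are often not standardized and are heavily reliant on stimuli availability", and of self-report that "one-time self-report measures may underestimate the prevalence of olfactory impairment". If the household rating is noisy, a good SSTT will predict it poorly. If the SSTT is the noisy one, the fit will be just as poor. A reader of the results could not tell these cases apart, yet the outcome is meant to guide which self-assessment approach to recommend.

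A smaller gap sits beside this. Statistical Analysis relates SSTT taste to self-rated taste but lists no such regression for SSTT smell on self-rated smell, although Daily Smell and Taste Testing collects that rating at every session.

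**Working it through.** The documents give no figure for this comparison, so there is no stated result to reproduce. The check is structural, followed by an illustration with assumed inputs.

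**1. Outcome against named analyses**

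| Analysis named | Instruments | What it gives |
|---|---|---|
| Linear regression | SSTT smell with household smell; SSTT taste with self-rated taste | Agreement |
| GCCRQ correlation | GCCRQ (optional) with study measures | Agreement |
| Factor analysis | SSTT alone, baseline | Consistency, no comparator |
| Logistic regression | Not named | Discrimination, against other symptoms |
| Mixed models | Not named | Group difference in acuity |

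No row gives consistency or discriminability per instrument with a difference between instruments.

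**2. Why the regression cannot rank the tests**

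Let both tests measure one trait T with independent errors, with reliabilities ρS (SSTT) and ρH (household). Then R² = ρS × ρH.

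- SSTT better: 0.9 × 0.5 = 0.45
- Household better: 0.5 × 0.9 = 0.45
- Equal: 0.67 × 0.67 = 0.449

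The standardized slope is √0.45 = 0.671. At n=235 the test statistic is 0.671 × √(233/0.55) ≈ 13.8. Both are unchanged when the reliabilities are swapped. Only the raw slope differs (0.90 against 0.50), and only if the tests share a unit. They do not: the SSTT uses a visual analog scale and the household test a scale from absent to heightened.

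**3. What a per-instrument analysis would show**

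Inputs:

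- n = 235: the minimum in Sample Size Determination.
- 20% swab-positive: assumed, borrowing the 0.20 in the power calculation, which is not a stated prevalence.
- Share of positives with loss: 52.7% (the pooled olfactory figure in the Introduction) or 22.6% (the Singapore cohort figure there).
- Size of loss 2 SD, no loss among negatives, reliabilities 0.9 and 0.5 among people without loss: assumed.

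*R² in the full sample at 52.7%.* The share with loss is 0.20 × 0.527 = 0.105. Var(T) = 1 + 4 × 0.1054 × 0.8946 = 1.377. Error variances are 0.111 and 1. R² = 1.377² / (1.488 × 2.377) = 0.536, whichever test is better.

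*AUC for true loss.* Φ(√(2ρ)) gives Φ(1.342) = 0.910 and Φ(1) = 0.841.

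*AUC against swab result.* Positives without loss look like negatives, so AUC = f × AUC(loss) + (1 − f) × 0.5.

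| Share f with loss | SSTT (ρ 0.9) | Household (ρ 0.5) | Difference | SD of paired difference, n=235 |
|---|---|---|---|---|
| 0.527 | 0.716 | 0.680 | 0.036 | 0.033 |
| 0.226 | 0.593 | 0.577 | 0.016 | 0.037 |

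The SDs come from simulating 6,000 studies per row. The difference had the wrong sign in about 13% of studies in the first row and 33% in the second.

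*Consistency.* The two-occasion retest correlation among people without loss is 0.9 against 0.5, a difference of 0.40. Its simulated SD was about 0.05.

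**The case against.** The strongest reply is that nothing in Statistical Analysis ties the regression to the methodological outcome. Relating a new test to an existing method is ordinary convergent evidence, and Study Overview speaks only of an initial validation. The factor analysis touches consistency, and the logistic and mixed models touch discrimination. The article is condensed, and Availability of Data and Materials promises a full protocol that may hold more.

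Much of this stands. The regression is a legitimate description of agreement, and the related analyses exist. What does not follow is that together they deliver the outcome. One covers the SSTT alone, two name no instrument, and the rest are agreement. The article states both the outcome and the analysis for this pair of tests, and the two do not match, so the point does not rest on detail left to a longer document.

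A reader might infer more than the text supports:

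- *That the SSTT is not compared with self-reported smell at all.* The Introduction announces a comparison with self-report, and the GCCRQ, which includes smell items, is to be correlated with study measures. Only the regression on daily self-rated smell is unlisted.
- *That the protocol calls self-report inaccurate.* It says such measures may not reflect the true extent of change, or may underestimate impairment.
- *That the stated aim is to prove the SSTT superior.* The outcome is a comparison; it still needs a value per test.
- *That the study would show a gap such as 0.91 against 0.84.* Those AUCs are for true loss, which is never observed. Against swab result the gap is about half that or less.

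**Conclusion.** The point holds in this form: the protocol names a comparison of consistency and discriminability as its primary methodological outcome, while the between-instrument analyses it names are of agreement only. Fit statistics from a simple regression are symmetric in the two tests, so they cannot show which is better. The symmetry of R², the standardized slope and the p-value is exact for any inputs; the product form needs one trait and independent errors.

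The sizes are illustrative and rest on the assumed reliabilities, the 2-SD loss and 20% positive. Under those inputs a per-instrument consistency contrast is well estimated at n=235. A single-day discriminability contrast against swab result is imprecise, because its difference (0.016 to 0.036) is about the size of its SD or smaller. This should be corrected before analysis. It does not invalidate the data, which can support the comparison.

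**What to change.** Change the Statistical Analysis wording as follows:

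- **Consistency.** For SSTT smell, household smell and daily self-rated smell, and for SSTT taste and self-rated taste, estimate day-to-day reliability (for example an intraclass correlation over daily sessions in participants reporting stable or unchanged acuity). Report paired differences between instruments with bootstrap intervals that resample participants.
- **Discriminability.** For each instrument, estimate the AUC or standardized difference between swab-positive and swab-negative participants in the same people, at the first session in which all are completed or pooled over early sessions. Report paired differences with the same kind of interval, as estimates rather than as a test expected to separate the instruments. Table 1 lists only the SSTT in clinic, which suggests that the first common session is at home; because the table has no household row, this should be confirmed.
- **Agreement.** Keep the regression, labelled as a description of agreement, and add SSTT smell against self-rated smell.

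The cost is analysis wording and some programming. The ratings are already collected daily from the same participants, and swab results are linked to them. The downside is the limited precision of the discriminability contrast, which the plan should state.
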